## Abstract

**Objectives:**

The general objective of this study is to test the hypothesis that administration of convalescent plasma from donors with previous diagnosis of severe COVID-19 pneumonia is safe and associated with a decrease in all-cause in-hospital mortality among hospitalized patients with COVID-19 at 30 days in comparison with standard treatment alone.

The secondary objectives are as follows: (1) to assess the efficacy of convalescent plasma to reduce the length of hospitalization, (2) to assess the efficacy of convalescent plasma to reduce the length of ICU stay, and (3) to assess the efficacy of convalescent plasma on reducing the requirement of invasive mechanical ventilation or ICU stay.

**Trial design:**

PERUCONPLASMA is a IIb phase open label, randomized, superiority clinical trial with 1:1 allocation taking place in real life routine clinical practice at public hospitals in Lima, Peru. Participants will be randomized to receive convalescent plasma along with local standard treatment or local standard treatment alone. After allocation, all participants will be followed for a total of 30 days or until hospital discharge, whichever occurs first.

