**Intervention and comparator:**

Convalescent plasma from donors with previous severe COVID-19 is the investigational medical product.

The experimental group will receive 1 to 2 units of 200 to 250 ml of convalescent plasma along with local standard treatment. The control group will receive local standard treatment alone. The participants randomized to plasma will have evaluations at 6 h and 24 h to specifically evaluate possible post transfusion events. All the participants will be evaluated at day 3, day 7, and day 30 after enrolment.

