**Main outcomes:**

Safety outcome:
Incidence of serious adverse reactions related to convalescent plasma transfusion within 24 h after convalescent plasma administration.

Efficacy outcomes:
Mortality from any cause during hospitalization at 30 days post randomization.Length of hospitalization at 30 days post randomization or until hospital discharge.Duration of mechanical ventilation at 30 days post randomization or until hospital discharge.Length of hospitalization in an intensive care unit at 30 days post randomization or until hospital discharge.

Exploratory:
Oxygen requirement evolution at days 3 and 7.Score Sequential Organ Failure Assessment (SOFA) evolution at days 3 and 7.Dynamics of inflammatory marker (lymphocyte, C-reactive protein (CRP), D-dimer, lactate dehydrogenase (LDH)) evolution at days 3 and 7.Proportion of patients progressing to multi-organ failure at 30 days post randomization or until hospital discharge.Proportion of transfusion related adverse reactions at 30 days post randomization or until hospital discharge.

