**Blinding (masking):**

Both the participants and study staff will be aware of the allocated intervention.

Blinded statistical analysis will be performed.

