**Numbers to be randomized (sample size):**

The sample size was calculated using the Fleiss formula with continuity correction to detect a mortality reduction from 50 to 20% between the two treatment arms with a confidence level of 95% and a power of 80%. Based on this information, a total of 45 patients per arm would be needed. After adjustment for a drop-out rate of 10% after enrolment, a total of 50 patients per arm (100 patients in total) will be enrolled.

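### Follow-up ends at discharge while a day-30 evaluation is planned for everyone, so deaths after discharge but before day 30 are not counted and the mortality comparison may be biased if the arms differ in them

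*Protocol article*

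**What the plan says.** Four statements in the protocol article bear on this point.

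- **Follow-up (Trial design):** "After allocation, all participants will be followed for a total of 30 days or until hospital discharge, whichever occurs first".
- **Visit schedule (Intervention and comparator):** "All the participants will be evaluated at day 3, day 7, and day 30 after enrolment".
- **Mortality outcome (Main outcomes, first efficacy outcome):** "Mortality from any cause during hospitalization at 30 days post randomization". The general objective matches it: a "decrease in all-cause in-hospital mortality among hospitalized patients with COVID-19 at 30 days".
- **Length of stay (Objectives, first secondary objective):** "to assess the efficacy of convalescent plasma to reduce the length of hospitalization".

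On masking, the article says: "Both the participants and study staff will be aware of the allocated intervention". The statistical analysis is to be blinded. The article never labels an outcome as primary, but mortality is the general objective, heads the efficacy list and drives the sample size, so it is treated here as the main outcome.

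**The concern.** A patient discharged on day 12 has no follow-up after day 12 under the Trial design section, yet is due an evaluation on day 30 under the intervention section. As worded, both cannot hold, and the choice between them decides whether day-30 vital status is known for discharged patients. The article provides nowhere for vital status after discharge.

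The second issue is what the outcome measures. A death counts only while the patient is in hospital, so the time in which a death can be observed depends on length of stay. The trial hypothesises that plasma changes length of stay, and allocation is known to participants and study staff. If stay shortens in one arm, in-hospital mortality can fall there with no change in 30-day survival. Blinding the analysis cannot recover deaths that were never recorded.

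**Working it through.** **1. The plan's own figure.** Inputs from the sample size section: a "mortality reduction from 50 to 20% between the two treatment arms", 95% confidence (taken as two-sided alpha 0.05), 80% power, Fleiss formula with continuity correction, 10% drop-out.

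- Uncorrected: n = [1.96·√(2·0.35·0.65) + 0.842·√(0.5·0.5 + 0.2·0.8)]² / 0.30² = (1.322 + 0.539)² / 0.09 = 38.5 per arm.
- Corrected: (38.5/4)·[1 + √(1 + 4/(38.5·0.30))]² = 44.9, so 45 per arm.
- Drop-out: 45/0.90 = 50 per arm.

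The stated 45 and 50 reproduce exactly and are not in dispute.

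**2. Bias under no true effect, by share of deaths missed.** The shares are assumptions. Let m be 30-day mortality in both arms and f the share of an arm's deaths that fall after discharge. The observed rate is m(1 − f). With observed rates a (control) and b (plasma) and 45 per arm, the chance of a significant result favouring plasma is Φ{[(a − b) − 1.96·s0]/s1}. Here s0 is the pooled and s1 the unpooled standard error.

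Worked case, m = 50%, f = 0% control and 10% plasma: a = 0.50, b = 0.45, s0 = 0.1053, s1 = 0.1051. The argument is (0.05 − 0.2063)/0.1051 = −1.487, which gives 6.9%.

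| m | f control | f plasma | Observed rates | Spurious benefit | Chance of false benefit |
|---|---|---|---|---|---|
| 50% | 10% | 10% | 45% v 45% | 0 points | 2.5% (nominal) |
| 50% | 0% | 5% | 50% v 47.5% | 2.5 points | 4.2% |
| 50% | 0% | 10% | 50% v 45% | 5 points | 6.9% |
| 20% | 0% | 10% | 20% v 18% | 2 points | 4.3% |

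The first row is the important limit: equal shares missed means no bias under the null.

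**3. Bias with equal risk after discharge but unequal discharge.** Assume 40% of control and 70% of plasma patients are discharged before day 30, and that each discharged patient has risk q of dying before day 30. The bias is q·(0.70 − 0.40). It is 0.3 points at q = 1% and 3.0 points at q = 10%. This case needs lower mortality than the planned 50%. With 70% discharged and q = 10%, total 30-day mortality can be at most 30% + 7% = 37%.

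**4. What one death does near the boundary.** With 50 per arm each uncounted death moves an arm's mortality by 2 points. Two-sided p-values for 25/50 control deaths against:

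| Plasma deaths | Pearson | Continuity-corrected | Fisher |
|---|---|---|---|
| 16/50 | 0.067 | 0.104 | 0.103 |
| 15/50 | 0.041 | 0.066 | 0.066 |
| 14/50 | 0.024 | 0.040 | 0.040 |
| 10/50 | 0.002 | 0.003 | 0.003 |

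Pearson crosses 0.05 between 16 and 15 deaths; the other two cross between 15 and 14. The counts were chosen to lie near the boundary. At the planned effect (25 v 10) the result is robust: if four plasma deaths had been missed, the true 25 v 14 would still give a corrected p of 0.040.

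**The case against.** The strongest reply is that the outcome is openly labelled. The objective says in-hospital, the outcome says during hospitalization, follow-up ends at discharge, and several other outcomes carry the same discharge limit. On that view the day-30 sentence is a visit schedule bounded by the follow-up rule, and one clarifying line settles it. The article is also a summary, and the full protocol may hold a scoring rule. It is fair that the authors stated their outcome and did not misreport it. But an accurate label does not stop the outcome depending on discharge timing, and the two sentences still conflict as printed.

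Three stronger readings are tempting and are not supported:

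- **That the rule favours the earlier-discharged arm as such.** Bias requires uncounted deaths that differ between arms. Shorter stay with plasma is a hypothesis, and if stay shortens through faster recovery, those sent home early may be at low risk.
- **That patients transferred or leaving against advice are scored as survivors.** The article mentions neither and gives no scoring rule for them.
- **That unblinded staff decide discharge.** The article says participants and study staff know the allocation, not who makes that decision.

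The objection on timing also stands in part. Recruitment began in September 2020 and was due to end in March 2021, with version 5.0 dated January 2021. Changing the main outcome that late in an open-label trial has a credibility cost and must be done openly.

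**Conclusion.** The point holds in conditional form. The follow-up rule and the day-30 evaluation conflict for anyone discharged before day 30, and the outcome as worded does not count a death after discharge. The mortality comparison can therefore be biased if discharge timing or post-discharge deaths differ between arms.

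The direction would favour plasma if plasma shortens stay and some of those discharged die before day 30. The size cannot be bounded from the document, because the follow-up rule stops collection of the data needed to bound it. The assumed inputs above give roughly 0.3 to 5 points and a chance of false benefit of up to about 7% in place of 2.5%. That is probably modest beside the planned 30 points. A reader might infer from the p-value table that one missed death would overturn the trial. The table shows that only for results already at the boundary.

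**What to change.** Reconcile the two sections so that every randomized participant is followed to day 30 regardless of discharge. Use the day-30 evaluation already planned to obtain vital status by phone or record check, including for participants already discharged.

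Analyse death from any cause within 30 days of randomization, wherever it occurs. Preferably make this the main outcome through a dated amendment, written without sight of outcome data by arm. At minimum prespecify it as a key sensitivity analysis. Report in-hospital mortality alongside it in either case.

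The sample size need not change: if 50% and 20% are read as 30-day mortality in any location, the requirement stays at 45, and 50 with drop-out, per arm. The costs are one contact or record check per participant discharged before day 30, the amendment with any approval or consent cover it needs, and a few participants of unknown status, to be handled by a sensitivity analysis.

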**Participants:**

The population for the study are patients with severe disease with a confirmed laboratory test for SARS-CoV-2 infection hospitalized in 3 tertiary-care hospitals in Lima, Peru.

Subjects are eligible for the trial if they meet all of the following inclusion criteria:
Age 18 or olderHospitalization due to COVID-19 with laboratory confirmation (either with serologic, molecular, or antigen test along with a compatible clinical presentation)Severe or critical COVID-19 disease

Severe illness was defined by 2 or more of the following:
Respiratory rate of 22 or moreHypoxemia with oxygen saturation equal or less than 93%Abnormal blood gas analysis (PaO_2_ < 60 mmHg, PaCO_2_ > 50 mmHg, or Pa/FiO_2_ < 300)

Critical disease was defined by either:
Mechanical ventilation requirement less than 72 h.Shock.4.Capacity to provide informed consent (patient or patient’s direct relative)5.Availability of convalescent plasma units compatible with ABO blood type of the subject.

Exclusion criteria:

Subjects are not eligible for the trial if they meet any of the following criteria:
Contraindication for transfusion (e.g., prior anaphylaxis, congestive heart failure)Hemodynamic instability (PA < 60 mmHg refractory to vasopressors)Uncontrolled concomitant infections\Stupor or comaPlatelets < 50,000/μL or disseminated intravascular coagulationSerum creatinine > 3.5 mg/dL or dialysis requirementTotal bilirubin > 6 mg/dL or jaundice of unknown etiologyMyocardial infarction or acute coronary syndromeActive or recent (< 7 days) intracranial hemorrhagePregnancy

Donors:

The donors have to meet the following criteria: male between 30 and 60 years with a previous diagnosis of severe COVID-19-associated pneumonia within the last 3 months, with resolution of symptoms of at least 28 days. The rationale for including donors with severe disease is to maximize the probability of collecting convalescent plasma units with high titer of neutralizing antibodies, as the technology to measure this specific type of antibodies is not routinely available in Peru. Aliquots of plasma will be stored for future quantification of neutralizing antibodies.

**Intervention and comparator:**

Convalescent plasma from donors with previous severe COVID-19 is the investigational medical product.

The experimental group will receive 1 to 2 units of 200 to 250 ml of convalescent plasma along with local standard treatment. The control group will receive local standard treatment alone. The participants randomized to plasma will have evaluations at 6 h and 24 h to specifically evaluate possible post transfusion events. All the participants will be evaluated at day 3, day 7, and day 30 after enrolment.

**Main outcomes:**

Safety outcome:
Incidence of serious adverse reactions related to convalescent plasma transfusion within 24 h after convalescent plasma administration.

Efficacy outcomes:
Mortality from any cause during hospitalization at 30 days post randomization.Length of hospitalization at 30 days post randomization or until hospital discharge.Duration of mechanical ventilation at 30 days post randomization or until hospital discharge.Length of hospitalization in an intensive care unit at 30 days post randomization or until hospital discharge.

Exploratory:
Oxygen requirement evolution at days 3 and 7.Score Sequential Organ Failure Assessment (SOFA) evolution at days 3 and 7.Dynamics of inflammatory marker (lymphocyte, C-reactive protein (CRP), D-dimer, lactate dehydrogenase (LDH)) evolution at days 3 and 7.Proportion of patients progressing to multi-organ failure at 30 days post randomization or until hospital discharge.Proportion of transfusion related adverse reactions at 30 days post randomization or until hospital discharge.

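### The hypothesis says plasma is safe, but the one outcome named as safety can occur only after plasma and so gives no comparison between arms

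*Protocol article*

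**What the plan says.** All references are to the protocol article.

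- **Objectives.** The general hypothesis is that plasma "is safe and associated with a decrease in all-cause in-hospital mortality among hospitalized patients with COVID-19 at 30 days in comparison with standard treatment alone".
- **Main outcomes, safety.** One outcome is listed: "Incidence of serious adverse reactions related to convalescent plasma transfusion within 24 h after convalescent plasma administration".
- **Main outcomes, exploratory.** A second reaction outcome covers a longer period: "Proportion of transfusion related adverse reactions at 30 days post randomization or until hospital discharge".
- **Intervention and comparator.** "The participants randomized to plasma will have evaluations at 6 h and 24 h to specifically evaluate possible post transfusion events". The visits common to both arms come later: "All the participants will be evaluated at day 3, day 7, and day 30 after enrolment".
- **Blinding.** Participants and study staff know the allocation. Only the statistical analysis is blinded.
- **Main outcomes, efficacy and exploratory.** Several outcomes do not depend on transfusion, among them "Mortality from any cause during hospitalization at 30 days post randomization" and "Proportion of patients progressing to multi-organ failure at 30 days post randomization or until hospital discharge". Duration of ventilation, ICU stay, oxygen requirement and SOFA are also listed. None of these is labelled as safety.

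**The concern.** Safety is stated as something the trial will test, yet the outcome chosen for it does not use the randomized control arm. Two features of the definition cause this. The event must be related to plasma, and its clock starts when plasma is given. Neither applies to a patient on standard treatment alone.

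This matters more here than in a healthier population. Participants have severe or critical disease, and their illness alone can produce respiratory or circulatory deterioration. When such a patient worsens after a transfusion, unblinded staff must decide whether plasma or COVID-19 was the cause. If they decide on COVID-19, the event leaves the safety outcome. If they decide on plasma, a background event may be counted as harm. A concurrent control arm removes the need for that judgement, and the definition gives it up. The 30-day reaction outcome lengthens the window but keeps the same attribution filter.

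At stake is the meaning of a conclusion that plasma is safe. On the named outcome, it would rest on an uncontrolled, attribution-dependent count in about 50 people.

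**Working it through.** **1. The plan's own figure.** Inputs from the sample size section: mortality 50% vs 20%, confidence level 95% (taken as two-sided), power 80%, Fleiss formula with continuity correction.

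- Uncorrected: n = [1.96·√(2·0.35·0.65) + 0.8416·√(0.5·0.5 + 0.2·0.8)]² / 0.30² = (1.322 + 0.539)² / 0.09 = 38.5.
- Corrected: (38.5/4)·[1 + √(1 + 4/(38.5·0.30))]² = 44.9, so 45 per arm.
- Drop-out of 10%: 45/0.9 = 50 per arm.

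The stated 45 and 50 reproduce. The size comes from mortality alone.

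**2. Which outcomes give a between-arm contrast.**

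| Outcome | Listed as | Can occur in a control? | Depends on attribution? |
|---|---|---|---|
| Serious plasma-related reactions, 24 h | Safety | No | Yes |
| Transfusion-related reactions, to day 30 or discharge | Exploratory | Not through plasma | Yes |
| All-cause in-hospital death | Efficacy | Yes | No |
| Ventilation duration, ICU stay | Efficacy | Yes | No |
| Oxygen requirement, SOFA, multi-organ failure | Exploratory | Yes | No |

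The single row designated as safety has no contrast. The rows with a contrast are not designated as safety.

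**3. What attribution can do to the count.** The article gives no serious adverse event rates, so these are assumptions. Suppose the true risk is 20% on standard treatment and 30% with plasma. In 50 plasma patients that is 50 × 0.10 = 5 extra events on top of 50 × 0.20 = 10 background events. If a share f of the extra events is attributed to plasma, an attribution-based count shows 5f of them: none at f = 0, all five at f = 1. If a share g of the background events is wrongly attributed, 10g are added. Neither f nor g can be estimated without a control arm, so the direction of the error is unknown.

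**4. Precision of the 24 h reaction rate.** With 0 events in n, the exact two-sided 95% upper limit is 1 − 0.025^(1/n) and the one-sided limit is 1 − 0.05^(1/n).

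- n = 50: 7.1% two-sided, 5.8% one-sided.
- n = 45: 7.9% two-sided, 6.4% one-sided.

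The chance of seeing at least one reaction in 50 is 1 − (1 − p)^50: 39.5% at p = 1%, 63.6% at p = 2% and 92.3% at p = 5%.

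These figures follow from the number of patients. They show how far a clean count can be taken, and do not measure the effect of lacking a comparator.

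**5. What a two-arm comparison could show with 50 per arm.** Two-sided 5% test, pooled variance under the null, assumed rates:

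| Control | Plasma | Power |
|---|---|---|
| 10% | 20% | 29% |
| 20% | 30% | 21% |
| 20% | 40% | 59% |
| 30% | 50% | 53% |

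The increase detectable with 80% power is about 10% to 33%, 20% to 46%, or 30% to 58%. For scale, with 20% in both arms the 95% CI for the risk difference has half-width 1.96·√(2·0.20·0.80/50) = 15.7 percentage points. This supports an interval estimate. It does not support a test or a claim of equal safety.

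**The case against.** The other side has several good points.

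- **Harm can be compared between arms.** A reader might infer that the trial cannot compare safety at all. The article does not support that. All-cause death, ventilation, ICU stay, oxygen requirement, SOFA and multi-organ failure are listed without reference to transfusion, and both arms share the visits at days 3, 7 and 30. Respiratory worsening would show in several of these, whatever cause staff assign. What remains is that none is designated as safety and no all-cause adverse event outcome is listed.
- **The extra plasma-arm checks look like unequal surveillance.** Checks at 6 h and 24 h are normal after a transfusion and are not an error. They would bias a comparison only if adverse events were compared as found at those checks, and the article describes no such analysis.
- **The objective may not promise a comparative safety test.** The comparison with standard treatment can be read as belonging to mortality alone. That is fair. Even so, safety is put forward as a hypothesis, and a reaction rate speaks only to transfusion reactions.
- **The article is a summary.** The full protocol, not shown here, may collect serious adverse events in both arms. Nobody can infer from the article that these data are missing. The point rests on a definition the article does state.
- **The 30-day outcome is not explicitly restricted to one arm.** It does not name plasma, so a control transfused for another reason could in principle count. It remains limited to transfusion-related events.
- **The remedy has little power.** This is true, and it is why estimation is proposed.

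**Conclusion.** The point holds as a limited one. The only outcome designated as safety is a plasma-arm count that depends on open-label attribution. It gives no between-arm estimate, and it loses harms read as disease progression. It cannot by itself support the statement in the objective that plasma "is safe and associated with a decrease in all-cause in-hospital mortality", as far as the safety part goes. At best, with no events in 50, it would say that serious 24 h reactions are unlikely to exceed 7.1% (two-sided 95%).

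The size of the attribution error cannot be calculated from the article. The serious adverse event rates used above are assumptions, and the comparison assumes that controls receive no plasma outside the trial. The stated sample size is correct for mortality and is not in question. This is a change worth making in how safety is defined and reported. It is not a flaw in the mortality comparison.

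**What to change.** 1. Add a safety outcome: all serious adverse events regardless of attribution, in both arms, from randomization to day 30 or discharge. Use the same definitions and the same ascertainment in both arms, with chart review for the period before the first common visit at day 3, so that the plasma-arm checks do not create unequal detection.
2. Report it as a risk difference with 95% CI, described as estimation. Do not read an interval that includes zero as evidence of equal safety.
3. Keep the 24 h transfusion-reaction rate as a descriptive plasma-arm figure with an exact CI, and limit any conclusion from it to transfusion reactions.
4. Word the safety part of the objective to match: estimate the difference in serious adverse events, and describe transfusion reactions.

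Cost: some extra data entry from the routine chart for control patients, with no new procedures and no change in sample size. If the full protocol already collects these events in both arms, only the outcome designation and the wording change.
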